## Abstract

**Introduction::**

*Gwakhyangjeonggi-san* (GJS) is an herbal formula with anti-inflammatory and anti-allergic properties that is broadly used to treat a wide range of diseases including gastrointestinal disorders and allergic diseases. There have been several clinical studies conducted on its effects on atopic dermatitis (AD). So far, no randomized controlled trials have been conducted. Here, we describe the protocol for a randomized controlled study designed to investigate the efficacy and safety of GJS for treating patients with AD that have gastrointestinal symptoms.

**Methods and analysis::**

A randomized, double-blind, placebo-controlled, parallel-group, clinical trial has been designed to investigate the clinical efficacy and safety of GJS on patients with AD that have gastrointestinal symptoms. A total of 58 participants with AD will be recruited and randomly allocated to the GJS or placebo group in a 1:1 ratio. The participants will be administered GJS or placebo granules 3 times a day for 8 weeks. Data will be collected from the participants at baseline and after 4 and 8 weeks. The primary outcome measure will be the mean change in the SCORing of Atopic Dermatitis (SCORAD) index from baseline to 8 weeks. The secondary outcomes will include the eczema area and severity index (EASI), dermatology life quality index (DLQI), EuroQoL 5 dimensions 5 levels (EQ-5D-5L), and immunological factors. The Korean Gastrointestinal Symptom Rating Scale (KGSRS), Nepean Dyspepsia Index will also be obtained for assessing the gastrointestinal status.

**Discussion::**

The findings of this study are expected to provide evidence on the safety and effectiveness of GJS and for treating patients with AD that have gastrointestinal symptoms. Additionally, the study will explore the mechanism of GJS action via gut microbiome. This study will provide new perspectives on approaching treatment for AD.

**Ethics and dissemination::**

The study protocol was approved by the Institutional Review Board of Kyung Hee University Korean Medicine Hospital at Gangdong (KHNMCOH2019-06-002-001).

**Trial registration number::**

This study has been registered at the Korean National Clinical Trial Registry, Clinical Research Information Service (KCT0004299).

## Introduction

1

Atopic dermatitis (AD) is a chronic, relapsing inflammatory skin disease that affects between 2.1% and 4.9% of adults and 20% of children around the world, but particularly in developed countries.^[1,2]^ AD is a complex and heterogeneous disease that is affected by various factors such as host genetics, altered skin barrier function, immunological abnormalities, and environmental factors, including exposure to specific pathogens.^[3]^

In recent years, gut microbiome has emerged as an important frontier in understanding the mechanism of AD.^[4,5]^ Recent evidence has demonstrated that dysbiosis of gut microbiota leads to a chronic progression of AD by dysregulation of gut inflammation and the gut epithelial barrier.^[6,7]^ Due to this evidence, it is expected that treatment that seeks to improve microbial composition is useful in the management of AD. Herbal drugs have been widely used for AD, based on their anti-inflammatory and anti-allergic properties.^[8]^ Recent studies have also shown the effects of herbal medicine on gut microbiota, which act as prebiotics to promote the growth of some gut microbiota species.^[9]^

*Gwakhyangjeonggi-san* (GJS), also known as *Huoxiang-zhengqi-san* in Chinese and *Kkako-shoki-san* in Japanese, is an herbal drug approved by the Ministry of Food and Drug Safety (MFDS) of the Republic of Korea. It is commercially marketed for anorexia, diarrhea, and fatigue^[10]^ and is used to treat a wide range of disorders, including gastrointestinal conditions^[11]^ and allergic diseases.^[12]^ GJS has demonstrated anti-inflammatory and anti-allergic activities in in vitro^[13]^ and in vivo studies.^[14]^ GJS was seen to improve AD symptoms and regulate serum cytokine levels in a clinical study.^[15]^ Moreover, GJS-probiotic combination treatment has been shown to be beneficial to gut microbiota counts.^[16]^ However, no randomized controlled trial has been conducted to report the efficacy and safety of GJS for AD in the view of the gut-skin axis.

Based on these previous studies, we hypothesize that GJS will improve the symptoms of AD by affecting gut microbiota, its related metabolites, and the immune system. This study aimed to observe the efficacy and safety of GJS in patients with moderate AD and gastrointestinal symptoms. Additionally, we will investigate the mechanism of the GJS action by analyzing immune biomarkers as well as microbiome in a randomized controlled experiment.

## Methods

2

### Objective

2.1

This protocol will be illustrated clinical trial design to investigate the efficacy and safety of GJS in patients with moderate AD concomitant with gastrointestinal symptoms and verify its mechanism via gut microbiome and immune biomarkers.

### Study design

2.2

This randomized, double-blind (patient, practitioner, and assessor), placebo-controlled, parallel-group, clinical trial will be conducted at the Kyung Hee University Korean Medicine Hospital at Gangdong (Seoul, Republic of Korea). A total of 58 participants will be recruited for this trial and participants will be assigned either GJS treatment group or placebo controlled group. The trial will consist of an 8-week oral administration of GJS with 2 visits at 4-week intervals. Before enrollment, all participants will undergo a 7-day run-in period. The enrolled participants will be randomly allocated to 2 parallel groups: the GJS group and the placebo group. The study design flow chart is shown in Fig. 1 and Table 1. This protocol is based on the Standard Protocol Items: Recommendations for Interventional Trials.

**Figure 1 F1:**
[figure not shown]
Study design flowchart. GJS = Gwakhyangjeonggi-san.

**Table 1 T1:**
[figure not shown]
Schedule of enrollment, interventions, and outcome measurements for a randomized controlled trial assessing the safety and clinical efficacy of *Gwakhyangjeonggi-san* (GJS) on moderate atopic dermatitis with gastrointestinal symptoms.

### Participants

2.3

#### Inclusion criteria

2.3.1

Participants will be considered eligible for inclusion if they meet the following criteria:

1.Men or women aged 19 to 60 years.2.Diagnosis of AD based on the Hanifin and Rajka diagnostic criteria, which require that ≥3 major features and ≥3 minor features be fulfilled.3.Diagnosis of gastroduodenal or bowel disorder based on the ROME IV Questionnaire.4.Moderate AD diagnosed by the SCORing of Atopic Dermatitis (SCORAD) index (score 25–50).5.Ability to comprehend the purpose of the study, the study procedure, and the properties of the investigational drug, as well as voluntary agreement to participate in the study (provision of written informed consent).

#### Exclusion criteria

2.3.2

The exclusion criteria will be as follows:

1.Diagnosis of concomitant skin disorders that make it difficult to accurately evaluate cutaneous symptoms of AD.2.Use of orally administered corticosteroids or antibiotics, administration of psoralen and ultraviolet A therapy or immune-suppressants within the last 4 weeks preceding screening visit.3.Use of medications including herbal preparations, dietary supplements, or probiotics for symptomatic improvement of AD within the last 4 weeks of screening.4.Diagnosis of serious medical conditions that could interfere with clinical trial participation, including the following:4-1.Uncontrolled hypertension (systolic blood pressure ≥160 mmHg and diastolic blood pressure ≥100 mmHg).4-2.Uncontrolled diabetes mellitus (HbA1c ≥6.5%).4-3.Abnormal kidney function test results showing serum creatinine levels >2-fold the upper limit of the reference range.4-4.Abnormal liver function test results showing serum alanine aminotransferase or aspartate aminotransferase levels >2-fold the upper limit of the reference range.4-5.Other serious inflammatory and systemic diseases.4-6.Past or present history of malignant tumors.5.Genetic disorders, such as galactose intolerance, Lapp lactase deficiency, or glucose-galactose malabsorption.6.Intake of other clinical trial drugs within a month preceding the start date of the investigational drugs for the present trial.7.Pregnancy, planning a pregnancy, or breastfeeding.8.Known history of hypersensitivity or allergic reaction to the investigational drug or its ingredients.9.Communication difficulties that prevent adequate compliance with the investigator's instructions.10.Ineligibility for participation determined by the investigator.

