#### Withdrawal criteria

2.3.3

1.Participants’ withdrawal of consent.2.Detection of eligibility violations.3.Occurrence of a serious adverse event.4.Use of prohibited medication.5.Pregnancy.6.Protocol violations during the study.7.Total medication compliance under 80%.8.Discontinuity of contact.9.Unsuitability as judged by the investigators.

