**Table 2 T2:**
[figure not shown]
Composition of the *Gwakhyangjeonggi-san* (GJS).

GJS and placebo granules are sealed in opaque aluminum bags and administered to participants in doses of 3 g. The pharmacists will instruct the participants to dissolve GJS or placebo from each package in water and take the solutions 3 times per day 30 minutes before breakfast, lunch, and dinner or between meals for 8 weeks. All participants will be requested to return remains of drugs for calculating compliance.

Participants who have been receiving medication for chronic diseases such as hypertension and diabetes mellitus prior to the initiation of this study will be allowed to continue their regimen if it is a medication unlikely to affect the results. Care will be taken not to alter the dosage or type of drug during the study. Participants of both groups will be prohibited from the concomitant use of medication such as steroids, antihistamines, and immunosuppressive drugs that can potentially affect the outcome of this experiment until after the 8-week follow-up.

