#### Safety outcomes

2.8.5

For the safety of the study participants, complete blood cell counts, liver function tests, lipid tests, and urine analyses will be performed at the screening phase and end of the trial. Vital signs will be examined at every visit. For female participants, urine human chorionic gonadotropin (hCG) will be checked at the screening visit to test for pregnancy. The investigator will ask about any expected or unexpected adverse events and record details of adverse events in the case report form (CRF). When serious adverse events occur, the investigator will immediately report this to the institutional review board (IRB) within 24 hours. If a serious adverse event occurs, the investigators will determine whether it is acceptable, whether the experimental drug should be continued or stopped, and whether the trial should be amended or ended.

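### Exclusion 4-1 requires both blood pressure limits to be reached, so a person far above only one of them is not excluded by the number; 'and' should be 'or'

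*Protocol article*

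**What the plan says.** Section 2.3.2 (Exclusion criteria), item 4, excludes people with "Diagnosis of serious medical conditions that could interfere with clinical trial participation, including the following". The first condition listed, item 4-1, is uncontrolled hypertension, defined as "systolic blood pressure ≥160 mmHg and diastolic blood pressure ≥100 mmHg".

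Other parts of the protocol article that bear on the point:

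- Item 4-4 of the same list sets a limit on two liver enzymes and joins them with 'or', so either one excludes.
- Item 4-5 adds "Other serious inflammatory and systemic diseases", and item 10 adds "Ineligibility for participation determined by the investigator". Neither gives a blood pressure value.
- Section 2.7 (Intervention) lets patients already on treatment for hypertension take part and continue it, provided the drug is unlikely to affect the results. It adds "Care will be taken not to alter the dosage or type of drug during the study".
- Section 2.8.5 (Safety outcomes) says "Vital signs will be examined at every visit", with no action limit stated. Section 2.9 adds telephone calls in weeks 2 and 6. Section 2.3.3, item 9, allows withdrawal for "Unsuitability as judged by the investigators".

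**The concern.** The label of item 4-1 names a condition, but the numeric rule covers only part of it. Someone with a very high systolic pressure and a diastolic just under 100 mmHg, or the reverse, does not meet the protocol's own definition.

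What is at stake is patient safety at entry. A numeric limit exists so that exclusion does not depend on who is screening. Under the present wording, two screeners could treat the same reading differently, and a monitor checking against the protocol would find no violation in admitting 185/95 mmHg. For the same reason, withdrawal for an eligibility violation (section 2.3.3, item 2) would not apply to that person. Because section 2.7 admits treated hypertensive patients, item 4-1 is the working numeric screen for that group.

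**Working it through.** **Step 1. The logic of the rule.** The inputs are the two limits in item 4-1, 160 and 100 mmHg. The readings are illustrations, not data from the article.

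| Reading (mmHg) | Excluded under 'and' (as written) | Excluded under 'or' |
|---|---|---|
| 165/105 | yes | yes |
| 180/95 | no | yes |
| 200/99 | no | yes |
| 150/110 | no | yes |
| 159/120 | no | yes |
| 150/95 | no | no |

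The two wordings differ exactly for people who reach one limit and not the other.

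**Step 2. The plan's own figure.** The article gives no figure for this point. The only number borrowed from it is 58, used below as a convenient scale. It reproduces from section 2.4: 23 / (1 − 0.20) = 28.75, rounded up to 29 per group, 58 in total. It does not depend on item 4-1.

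**Step 3. How many people the difference covers.** The article gives no blood pressure distribution, so these inputs are assumptions: systolic and diastolic pressure in hypertensive applicants are bivariate normal, with means 140/88 to 145/90 mmHg, SDs 15 and 10, and correlation r of 0.5 to 0.7.

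With S = P(systolic ≥160), D = P(diastolic ≥100) and B = P(both):

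- P(exactly one limit) = S + D − 2B
- P(at least one limit) = S + D − B
- P(far above one, below the other) = P(systolic ≥180 and diastolic <100) + P(diastolic ≥110 and systolic <160)

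| Mean | r | S | D | B | Exactly one | At least one | Exactly one / at least one | Far above one, below the other |
|---|---|---|---|---|---|---|---|---|
| 140/88 | 0.5 | 0.091 | 0.115 | 0.033 | 0.139 | 0.173 | 81% | 0.0087 |
| 140/88 | 0.7 | 0.091 | 0.115 | 0.048 | 0.110 | 0.158 | 70% | 0.0043 |
| 145/90 | 0.5 | 0.159 | 0.159 | 0.063 | 0.192 | 0.255 | 75% | 0.0129 |
| 145/90 | 0.7 | 0.159 | 0.159 | 0.084 | 0.149 | 0.233 | 64% | 0.0055 |

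**Step 4. Scale to 58 applicants.** With a hypertensive share h of 5% to 20% (also assumed), the expected number is 58 × h × P.

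- Exactly one limit: 58 × 0.05 × 0.110 = 0.32, up to 58 × 0.20 × 0.192 = 2.23.
- Far above one, below the other: 58 × 0.05 × 0.0043 = 0.012, up to 58 × 0.20 × 0.0129 = 0.150.

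The absolute numbers are small. Under these assumptions, though, the rule as written misses 64% to 81% of the people an 'or' rule would catch.

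**The case against.** The strongest reply concerns weight, since the wording itself is not in dispute.

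- **Other routes to exclusion exist.** Item 4 is an open list, and a person at 200/99 mmHg could be excluded under it, under item 4-5 or under item 10. This is true, and such a person is not automatically eligible. But all three routes need clinical judgement and none sets a blood pressure value.
- **The numbers are small and assumed.** The group that matters most for safety is 0.01 to 0.15 people per 58 applicants. The larger figure includes marginal readings just over one limit. In addition, 58 is the number to be recruited and randomised, while the number screened is not given. All of this stands, and it keeps the point minor.
- **No blood pressure hazard is shown.** The article describes the study drug as approved and marketed and names no such risk. That stands. The argument is that an entry limit should do what its label says; it does not claim that the drug raises blood pressure.
- **Safeguards follow after entry.** Vital signs, calls and withdrawal for unsuitability do help, but they act mainly once the person has been admitted, and no blood pressure threshold is attached to them. The section 2.7 statement about keeping existing drugs stable concerns people already on treatment and does not prohibit changes, so it does not alter the assessment.
- **It may be a drafting slip.** Item 4-4 suggests that 'either' could have been meant, and the full approved protocol (version 1.4) is not shown and may read differently. That is possible, but the printed criterion requires both limits and needs correcting if either was intended.

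**Conclusion.** The concern holds. As printed, item 4-1 excludes only people at or above both limits, and the article has no other numeric blood pressure rule. Those above one limit are kept out only if the investigator so judges.

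That conclusion rests on the text alone. Its size rests on the assumed blood pressure distribution and the assumed 5% to 20% hypertensive share, and it is low: about 0.3 to 2.2 people over exactly one limit per 58 applicants, and well under one person far above a limit. The consequence is confined to safety and consistency at entry. Sample size, power, type I error and the primary analysis are unchanged.

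**What to change.** In section 2.3.2, item 4-1, replace 'and' with 'or', so that systolic pressure of at least 160 mmHg or diastolic pressure of at least 100 mmHg excludes on its own. Apply the rule at screening. If the full protocol already uses 'or', only the article needs correcting.

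The cost is a one-word amendment and a few extra screen failures, about 0.3 to 2.2 per 58 applicants under the assumptions above. Section 2.11 requires approval of any modification by the ethics board and the Korean regulator. Recruitment began in September 2019 (section 2.5), so the changed rule would apply only to people screened after approval.

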#### Withdrawal criteria

2.3.3

1.Participants’ withdrawal of consent.2.Detection of eligibility violations.3.Occurrence of a serious adverse event.4.Use of prohibited medication.5.Pregnancy.6.Protocol violations during the study.7.Total medication compliance under 80%.8.Discontinuity of contact.9.Unsuitability as judged by the investigators.

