#### Atopic dermatitis symptoms

2.8.1

Disease severity and quality of life will be assessed using SCORAD, the eczema area and severity index (EASI), the Dermatology Life Quality Index (DLQI), and EuroQoL 5 dimensions 5 levels (EQ-5D-5L), respectively. The primary outcome of the present study is the difference between the SCORAD of the 2 study groups before (week 0) and after (week 8) medication has been administered. SCORAD, EASI, DLQI, and EQ-5D-5L also will be assessed at week 0, 4, and 8.

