### Statistical analysis

2.10

The measured variables, including the primary and secondary outcomes, will be assessed using the full analysis set based on the intention-to-treat principles. The per-protocol analysis set will be used for the sensitivity analysis. The baseline characteristic values in both groups will be expressed as a mean and standard deviation for continuous variables that are normally distributed or medians and interquartile ranges for non-normal data. Frequencies and percentages will be used to present categorical variables. Baseline differences between groups will be assessed using an independent 2-sample *t* test or Wilcoxon rank-sum test for continuous variables. The Chi-square test or Fisher exact test will be used for categorical variables. A mixed-effect model repeated measure (MMRM), which sets participants as a random factor and the group and visit as fixed factors, will be performed to analyze the between-group differences in the primary and secondary outcome measures. The Student paired *t* test and repeated-measures analysis of variance (ANOVA) will be used to evaluate the intra-group time changes in continuous values. Chi-square or Fisher exact tests will be used to evaluate the intra-group time changes in categorical values. MMRM does not require the replacement of missing data, and the missing data in the intra-group analysis will be replaced using the last observation carried forward method. The level of significance will be set at 0.05 (2-tailed). All analyses will be performed by an independent statistician using SAS version 9.4 (SAS Institute Inc., Cary, NC).

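### Four per-protocol-type grounds for withdrawal can cost the week-8 SCORAD, at odds with the intention-to-treat analysis

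*Protocol article*

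**What the plan says.** Section 2.3.3 of the protocol article is a list of nine withdrawal grounds. Four of them concern eligibility, adherence or conduct: "Detection of eligibility violations", "Use of prohibited medication", "Protocol violations during the study" (not limited to major ones) and "Total medication compliance under 80" per cent. The same list holds withdrawal of consent, loss of contact, pregnancy, serious adverse events and investigator judgement. It does not say whether withdrawal means stopping the granules, leaving the study, or both.

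Section 2.7 says that compliance is calculated from returned drug. It prohibits steroids, antihistamines and immunosuppressants until after the 8-week follow-up.

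Section 2.8.1 makes the week-0 to week-8 difference in SCORAD the primary outcome, with SCORAD measured at weeks 0, 4 and 8.

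Section 2.10 states that the primary and secondary outcomes "will be assessed using the full analysis set based on the intention-to-treat principles". It adds: "The per-protocol analysis set will be used for the sensitivity analysis". For the between-group model it notes that "MMRM does not require the replacement of missing data".

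**The concern.** An intention-to-treat analysis compares participants as randomised, whatever their later adherence or deviations. The four grounds above are the kind that normally define a per-protocol set. Used as grounds for withdrawal, they can end collection of the primary endpoint for exactly the participants whom intention-to-treat is meant to keep.

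The losses would not be random. Prohibited steroids or antihistamines are likely to be taken because the eczema is worse, and poor compliance may follow lack of benefit or poor tolerability. Missing week-8 values could therefore depend on outcome and on arm. A mixed model without imputation is valid only if the missing values are predictable from the observed ones. The named sensitivity analysis leaves out largely the same participants, so agreement between the two results would give little reassurance.

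**Working it through.** **1. The plan's own figure.** Section 2.4 gives 23 per group and 20% dropout: 23 / (1 − 0.20) = 28.75, rounded up to 29 per group and 58 in total. This reproduces. The allowance is 58 − 46 = 12 participants (20.7%) for all dropout. It is not a rate for the four grounds, and the article gives none. All rates below are assumptions.

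**2. When the compliance rule takes effect.** Three doses a day for 8 weeks is 3 × 7 × 8 = 168 doses, and 20% of that is 33.6. Total compliance is fully known only when treatment ends, although a breach becomes certain once 34 doses are missed.
- If the breach is found early, for example from a count at week 4, withdrawal can forgo the week-8 SCORAD.
- If it is found at the end, the week-8 SCORAD may already exist. Withdrawal then either changes nothing or sets a measured value aside, and the article does not say which.

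**3. How close the week-8 data come to the per-protocol data.** Assume 10% ordinary dropout and a further 5% to 15% withdrawn on the four grounds (58 × 0.05 = 2.9 to 58 × 0.15 = 8.7 participants).
- Week-8 values if these participants are still followed: 58 × 0.90 = 52.2.
- Week-8 values if they are not: 58 × 0.85 = 49.3 down to 58 × 0.75 = 43.5.

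The second line is also the number of per-protocol completers. At week 8 the two analyses then use essentially the same observations. They still differ at weeks 0 and 4, where withdrawn participants contribute to the mixed model.

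**4. Direction: non-compliers lost.** Suppose a fraction q in each arm does not comply, gains no benefit and is otherwise similar. The intention-to-treat effect is (1 − q) times the effect in compliers, so a retained-only estimate is too large by 1 / (1 − q):
- q = 0.10: 1 / 0.90 = 1.11
- q = 0.20: 1 / 0.80 = 1.25

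Week-4 data in the mixed model would tend to soften this.

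**5. Direction: users of prohibited medication lost.** Assume 25% on placebo and 15% on GJS are withdrawn, each 5 to 10 SCORAD points worse at week 8 than the observed data predict.
- Deterioration left out on placebo: 0.25 × 5 = 1.25 to 0.25 × 10 = 2.5 points.
- Deterioration left out on GJS: 0.15 × 5 = 0.75 to 0.15 × 10 = 1.5 points.
- Difference: 0.5 to 1.0 point.

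Placebo looks too good, so GJS is understated. This is opposite in sign to step 4.

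**6. How far the mixed model repairs the loss.** Assume no difference between arms within compliers or within non-compliers, with 15% (GJS) and 5% (placebo) withdrawn for non-compliance. Let non-compliers be 5 points worse at week 4 and 10 points worse at week 8, and let week 8 regress on week 4 with slope 0.6. The arm difference (positive means GJS worse) is:
- everyone followed: (0.15 − 0.05) × 10 = 1.0
- compliers only: 0
- week 8 predicted from week 4 for the withdrawn: (0.15 − 0.05) × 0.6 × 5 = 0.3

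In this example the model-based answer lies nearer the per-protocol result (0) than the fully followed one (1.0).

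**The case against.** The strongest reply is that the conflict is inferred. Section 2.3.3 is a bare list. It does not say that withdrawn participants miss later visits, that their data are discarded or that they leave the full analysis set. Section 2.10, the only text on analysis sets, keeps the full analysis set apart from the per-protocol set. The article condenses a longer protocol, which may provide for follow-up after withdrawal.

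Much of this stands. A reader might infer that the full analysis set nearly coincides with the per-protocol set. The documents do not support that: participants with week-0 and week-4 SCORAD remain in the mixed model, and only the week-8 data converge. A reader might also infer that the result is biased in favour of GJS. Steps 4 and 5 of the working point in opposite directions, and both rest on assumed inputs. A missing-data sensitivity analysis such as a tipping-point analysis commonly belongs in the statistical analysis plan, so its absence here is no fault.

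It is also fair to say that week-8 SCORAD after prohibited medication partly reflects that medication, so including it is a choice of estimand. It is, however, the choice that the stated intention-to-treat principle implies.

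The objection does not remove the point. The article does more than omit a detail: it places eligibility, adherence and conduct criteria in the same withdrawal list as loss of contact, and nothing in it reconciles that list with section 2.10.

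**Conclusion.** The point holds as a stated rule that fits badly with the stated analysis. Applied as written, the four grounds put week-8 SCORAD at risk for reasons related to adherence and outcome, and they weaken the per-protocol analysis as a check.

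Under the assumed 5% to 15% rate, about 3 to 9 of 58 week-8 values are affected. The bias illustrations run to a factor of 1.11 to 1.25 in one direction and to 0.5 to 1.0 SCORAD point in the other. The true rates are unknown and the net direction is undetermined. The documents do not show that data will in fact be discarded, so this is a correction worth making at low cost and not proof that the primary result would be invalid.

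**What to change.** Reconcile sections 2.3.3 and 2.10:
- State that eligibility violation, prohibited medication, protocol violation and compliance under 80% do not by themselves end outcome collection.
- Collect week-4 and week-8 SCORAD at the scheduled visits on every randomised participant unless consent is withdrawn or contact is lost.
- Keep those values in the full analysis set.
- Use the four criteria only to define the per-protocol set.

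Whether study drug stops in each case remains with the clinical team.

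The cost is amended wording and a few more completed visits that are already scheduled; N stays at 58. Some week-8 values will reflect prohibited medication, so the estimate becomes a treatment-policy effect. It could be smaller or larger than the estimate without those values.
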